### Analysis plan

#### Intention to treat

For our primary and secondary outcomes, we will estimate an intent-to-treat effect of the programme. Our design is the same as a CRCT stratified by EC. As such, we follow the standard estimation technique for two-way stratified CRCTs, For the outcome variable *Y* of individual *i* in district *j* at date *t,* we estimate the following:

$$Y_{ijt}=\mu +\gamma_{t}+\theta Treatment_{ijt}+\beta X_{ijt}+\varepsilon_{ij}$$

Where $\gamma_{t}$ is an evaluation cohort fixed effect, $Treatment_{ijt}$ is binary indicator variable equal to 1 if individual *i* is in a treatment district at date *t*, $X_{ijt}$ is a set of control variables. The treatment effect we identify is θ, and SEs will be clustered at the school level.

We will compute the Romano-Wolf stepdown p values to adjust for multiple hypothesis testing. Hypotheses will be arranged within families of outcomes—that is, each set of research questions separately.

The set of controls $X_{ijt}$ will be identified using a double-lasso procedure of the covariates we collect as part of our data collection. We will present estimates of the treatment effect both with and without these control variables. In addition to those controls that the double-lasso procedure generates, we will use (at a minimum) the following controls:

Mother’s age (quadratically).Mother’s educational attainment.Tester fixed effects (where relevant).Time between baseline and endline measurements.Child’s age.Child’s sex at birth.Baseline value of the outcome variable of interest.

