**Methods and analysis:**

This study is a cluster randomised controlled trial, in which the order that districts receive the programme is randomised. A minimum sample of 3240 children and 360 schools will be recruited across 72 district school cohort pairs. The primary outcomes are (1) child cognitive and socioemotional development measured using the International Development and Early Learning Assessment tool, the Strengths and Difficulties Questionnaire, and tasks from the Harvard Laboratory for Development Studies; (2) child health (measured using height/weight for age, height-for-weight Z scores). Secondary outcomes include (1) maternal mental health, (using Kessler-10 and Warwick Edinburgh Mental Wellbeing Scale) and knowledge of ECCE practices; (2) teacher knowledge, motivation and teaching quality (measured with classroom observation); (3) parental investment (using the Family Care Index and Home Observation Measurement of the Environment and the Child–Parent Relationship Scale); (4) water, sanitation, and hygiene (WASH) practices; (5) acute malnutrition (using mid-upper arm circumference). We will estimate unadjusted and adjusted intent-to-treat effects.

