**Figure 1 F1:**
[figure not shown]
Conceptual framework underpinning the Lively Minds intervention. KG, kindergarten; PS, play schemes.

The programme is owned and implemented by the Ghana GES. This is a key difference between the version of the programme evaluated in the efficacy trial and the current version. At that time, the programme was owned by the NGO Lively Minds who engaged the GES in implementation but remained in the driving seat throughout, retaining control over programme content and implementation strategy and leading on all aspects of programme implementation and monitoring on the ground. Control and responsibility for all of these elements have now been transferred to GES. Lively Minds provides technical assistance; for example, it helps districts set up the necessary monitoring and accounting databases, attends key training sessions of district teams and KG teachers, responds to queries from the GES Working Group in charge of the programme and accompanies the district officials to some of the monitoring visits.

Implementation is conducted at the district level, that is, once a district is enrolled in the programme, all of the KGs in the district are invited to participate. Before enrolment of districts begins, NGO Lively Minds familiarises the regional GES office (there are currently 16 regions in Ghana made up of 261 districts) with the Lively Minds Programme and trains a team tasked with mobilisation of the districts. Following this, there are five main implementation stages starting from enrolment of the district into the programme. These are summarised in figure 2. Online supplemental material S1 provides a more detailed explanation of what each step entails.

10.1136/bmjopen-2022-061571.supp1Supplementary data

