### Trial design

This study is an open-label CRCT, accommodating the phased and complete roll-out of the GES-LM Programme. The programme will be scaled to all of Northern Ghana’s 60 districts over 10 phases; each phase (equivalent to one school term) covering a district group (DG) of six districts, from September 2021 to September 2024 (figure 3A). Researchers at the the Institute for Fiscal Studies (IFS) randomised districts to DGs using R V.4.1.1. DGs will be enrolled into the evaluation study from January 2022 to September 2024 (hence, leaving out DG1) in six evaluation cohorts (ECs) (figure 3B). In each EC, one DG is allocated at random into the treatment group and one to the control DG. DG6 and DG7 are used first as control and later as treatment DGs, relying on different cohorts of children (those starting school in 2022 and those in 2023) (in different schools). DG10 will provide the control group for EC5 and EC6 using different schools. Control DGs will begin to receive the programme three terms after being enrolled into the study, after endline data collection has been completed (with the exception of EC6, where control will receive the programme after two terms). Baseline data collection will start at the end of January 2022 (after participant enrolment) (figure 3C). Data collection will proceed continuously through to the end of the project in early 2025. Figure 4 shows this design in a flow diagram, while figure 5 shows the participant timeline.

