### Sample size and power

As our design does not deviate in a substantive way from a conventional two-arm CRCT, we use standard CRCT methods to assess statistical power. For the power analysis, we consider the district as a cluster, providing us with 54 clusters. We consider the full sample size of 2,880 children (5 school per district-cohort, 8 children per school). We leverage data available from the efficacy trial to better inform how covariates increase our power to detect effects, including expected loss to follow-up, which we set at 6%.

We calculate minimum detectable effects (MDEs) using the following formula^28^:

(1)
$$MDE={\left(\frac{{\left(t_{\frac{\alpha }{2}}+t_{\beta }\right)}^{2}\sigma^{2}(m\rho \left(1-R_{c}^{2}\right)+\left(1-\rho \right)\left(1-R_{p}^{2}\right)}{n}\right)}^{\frac{1}{2}}$$

α denotes the significance level, β power, ρ unconditional intracluster correlation (ICC), *t* is the critical value of the t-distribution, σ is the SD of the outcome, *n* is children per arm, *m* is children per cluster, $R_{c}^{2}$ is proportion of cluster-level variance component explained by covariates and $R_{p}^{2}$ is the individual equivalent. One can interpret the effect of $R_{c}^{2}$ and $R_{p}^{2}$ as altering the ‘variance inflation factor’ of the power calculation—when they equal zero, the formula reduces to the standard CRCT one. We set α to 0.05, β to 0.8.

We estimate the ICC for each outcome data using data from the efficacy trial (ranging from 0.011 to 0.110). Note that we cannot conduct the same exercise for all of our primary outcomes, as some were not included in the original trial. The MDEs for some of our primary and secondary outcomes measured at the child/household level are shown in table 1. The power to detect effects at the school level is significantly more limited.

**Table 1 T1:** Minimum detectable effects (MDEs)

Outcome	MDE
Cognition factor score	0.110
Middle upper arm circumference	0.137
Knowledge Infant Development Index	0.119
Family Care Index	0.210
Parent–child interaction (Child–Parent Relationship Scale)	0.126

Each outcome controls for its baseline value only.

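### Districts are randomised but standard errors are clustered by school, so the tests omit the correlation between schools in a district and reject too often

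*Protocol article*

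**What the plan says.** All references are to the protocol article.

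- **Unit of randomisation.** The Abstract describes a cluster trial "in which the order that districts receive the programme is randomised". Under Trial design, the researchers "randomised districts to DGs using R V.4.1.1", that is, to district groups (DGs) of six districts, and "In each EC, one DG is allocated at random into the treatment group and one to the control DG".
- **Unit of delivery.** Intervention description: "Implementation is conducted at the district level", with every kindergarten in an enrolled district invited.
- **Unit in the power calculation.** Sample size and power: "For the power analysis, we consider the district as a cluster, providing us with 54 clusters".
- **Unit in the analysis.** Intention to treat regresses the outcome on an EC fixed effect, a treatment indicator and controls, and then states that "SEs will be clustered at the school level". It gives no reason for choosing the school, and no district effect or district-level alternative.
- **Re-use of districts.** Trial design: "DG6 and DG7 are used first as control and later as treatment DGs", and DG10 supplies controls for both EC5 and EC6, each time with different schools.

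**The concern.** All schools in a district receive the same assignment at the same time. They also share a district education office, which trains and supervises. The protocol itself lists differences in delivery quality between districts as a challenge and plans a survey of district officials. Outcomes in schools of one district should therefore be expected to correlate.

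School-clustered standard errors allow for correlation inside a school but set the covariance between schools of the same district to zero. EC fixed effects do not repair this, because they remove differences between cohorts and not differences between the 12 district-cohorts within one. The between-district variance is not lost altogether, since it is part of each school's total. What is lost is the part shared by the five schools.

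The clustering rule applies to every primary and secondary intention-to-treat estimate. If it understates the standard error, confidence intervals are too narrow and a programme with no effect has a raised chance of being reported to the government as effective at scale. The minimum detectable effects (MDEs) in Table 1 also describe a different test from the one to be run.

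**Working it through.** **1. The plan's own counts.** "The programme will be scaled to all of Northern Ghana’s 60 districts over 10 phases", six per phase. Leaving out DG1 gives 60 − 6 = 54 districts. Six ECs × 2 DGs × 6 districts = 72 district-cohorts; × 5 schools = 360 schools; × 8 children = 2,880 children. These match the power section. (The Abstract's 3,240 would be nine per school; I use the power section's figure.)

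**2. Which cluster Table 1 rests on.** Single MDEs cannot be reproduced, because the ICC and R² for each outcome are not given, but they can be bounded. I set R² = 0, 6% loss (n = 1,440 × 0.94 = 1,353.6 per arm), alpha 0.05 and power 80%. I add a factor of 2 for a difference between two arms, which formula (1) as printed lacks:

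MDE = (t for α/2 + t for power) × √[2(mρ + 1 − ρ)/n]

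| Cluster | m before loss | MDE at ρ = 0.011 | MDE at ρ = 0.110 |
|---|---|---|---|
| District (54) | 53.3 | 0.136 | 0.278 |
| School (360) | 8 | 0.112 | 0.142 |

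Table 1 gives 0.210 for the Family Care Index. School clustering cannot reach that even at the largest ICC with no covariates; district clustering can. Without the factor of 2, the maxima are 0.196 (district) and 0.100 (school). School clustering is then further still from 0.210, and the district maximum also falls just short, which suggests the missing 2 is a printing slip.

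**3. Type I error, all correlation at district level.** With 40 children per district-cohort (5 × 8) and district ICC ρ, the variance of the effect estimate is proportional to 1 + 39ρ. School clustering (8 per school) estimates it as 1 + 7ρ. The true two-sided error is 2[1 − Φ(1.96/√ratio)].

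| ρ | 1 + 39ρ | 1 + 7ρ | Ratio | True SE / reported SE | Type I error |
|---|---|---|---|---|---|
| 0.011 | 1.429 | 1.077 | 1.33 | 1.15 | 8.9% |
| 0.05 | 2.95 | 1.35 | 2.19 | 1.48 | 18.5% |
| 0.110 | 5.29 | 1.77 | 2.99 | 1.73 | 25.7% |

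The value 0.05 is an illustration inside the plan's range. With 6% loss (37.6 per district-cohort) the error rates are 8.7%, 18.0% and 25.2%.

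**4. Allowing for re-used districts.** Let r be the correlation of a district's effect between its two cohorts. With 36 district-cohorts per arm, the true variance is

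((72 − 12r)/1296)ρ + 2(1 − ρ)/1440.

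The 12 districts of DG6 and DG7 appear once in each arm and contribute −24r. The 6 districts of DG10 appear twice as controls and contribute +12r. The net effect, −12r, lowers the true variance. The school-clustered variance is (2/180)(ρ + (1 − ρ)/8). At ρ = 0.110 and r = 1 the true variance is 0.00509 + 0.00124 = 0.00633 against 0.00246. The ratio is 2.57 and the error 22%, against 25.7% at r = 0. At ρ = 0.011 and r = 1 the error is about 8%.

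**5. Simulation under no effect.** Two independent simulations used 6 ECs, 54 districts with DG6, DG7 and DG10 re-used, and 5 schools × 8 children. Figure 3 is not available, so the pairing of DGs to ECs was assumed.

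| District ICC | School-clustered, 8,000 runs per scenario | School-clustered, 6,000 runs per setting |
|---|---|---|
| 0.011 | 7.8–9.1% | 8.1% |
| 0.05 | 16.7–18.5% | 16.7% |
| 0.110 | 23.7–26.9% | 23.1% |

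In both, clustering by district brought rejection to about 6–7%. With no district variance (school ICC 0.05 only), school clustering rejected 5.0%, as it should.

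**6. If only a share f of the ICC lies between districts.** The ratio becomes (1 + 7ρ + 32fρ)/(1 + 7ρ).

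| Share f | ρ = 0.011 | ρ = 0.05 | ρ = 0.110 |
|---|---|---|---|
| 10% | 5.4% | 6.4% | 7.3% |
| 25% | 5.9% | 8.5% | 10.9% |
| 50% | 6.9% | 12.0% | 16.5% |
| 100% | 8.9% | 18.5% | 25.7% |

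**The case against.** The case on the other side concerns size, because no part of the protocol defends the choice of the school.

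- **The ICC may not be a district ICC.** The protocol does not say at what level it was estimated in the efficacy trial. Placing all of it between districts is the adverse end of the range. This stands, and the last table in the working shows the rates for smaller shares. The power section does, however, use the same ρ with the district as cluster.
- **Covariates may absorb district differences.** The adjusted model includes the baseline outcome, tester effects and lasso-selected controls, none of which is in the calculations above. This also stands as a reason for smaller inflation in the adjusted analysis. It removes the problem only if the controls take up all district variance, and it does nothing for the estimates without controls, which will also be presented.
- **Re-use of districts works partly the other way.** Correct: DG6 and DG7 in opposite arms lower the true variance by more than DG10 raises it. The formula and both simulations allow for this, and the inflation remains.
- **The Romano-Wolf p values are affected only if resampling is also by school.** The protocol does not state the resampling unit, so that part is conditional.
- **District clustering is not exact either.** It rejected about 6–7% in simulation, so at ICC 0.011 the gain is about two percentage points. This is a reason to add a small-sample correction, not to stay with schools.

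**Conclusion.** The concern holds. The stated standard-error rule contradicts both the randomisation and the power calculation, and the tests are anti-conservative for any positive district ICC that remains after adjustment. If the plan's ICC range applies at district level, true type I error is about 8–9% at the bottom of the range and 22–27% at the top, across the formulas and both simulations. If only a quarter to a half of it lies between districts, the range is 5.9% to 16.5%. These figures refer to the model without controls. The direction does not depend on the share; the size does, and the protocol does not give the district ICC separately. This must be changed before analysis, because one sentence governs every intention-to-treat test.

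**What to change.** Replace the sentence in the Intention to treat section with wording such as:

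> *Standard errors will be clustered by district (54 districts, one identifier per district across all evaluation cohorts), with a small-sample correction or a wild cluster bootstrap. Romano-Wolf resampling will draw whole districts.*

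Randomisation inference over the order of district groups can be added as a check. School-level correlation may be modelled inside the district but should not be the only level.

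The cost is a sentence of text and a modest change to the code, slightly more for the bootstrap and district-level resampling. No new data are needed. Intervals widen, by a factor of about 1.15 to 1.73 if the full ICC range is at district level. The power section already takes the district as the cluster, so this loses no precision that it had counted on.

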#### Heterogeneity

We will explore heterogeneity in treatment effect in two distinct ways.

We are first interested in considering treatment heterogeneity by baseline characteristics of the child, their home environment, and features of the environment at the preschool and district level. Given the large number of relevant dimensions, we will use recent methodological advances^29^ to assess heterogeneity across all of these dimensions in a rigorous and data-driven way.

Second, we will assess how study impacts vary by implementation fidelity and compliance in different dimensions. Given intervention fidelity measures are only observed in treatment districts, we will also examine heterogeneity from the data collected as part of the district official survey, focusing on those covariates that are most predictive of high fidelity in treatment districts.

#### Stopping rules

While there is always a risk of unintended consequences in all types of trials, in this sort of intervention, such a risk is minimal. However, if there is any clear evidence of harm, then the study will halt under international ethical guidelines for medical research.

#### Additional analysis

This is a large study with many collaborators, and the data gathered will be able to answer more scientific questions than those outlined in this protocol. The study team expects to conduct and publish such additional analyses.

#### Patient and public involvement

Patients or the public were not involved in the design of our research.

## Ethics and dissemination

The trial is overseen by the University College London Research Ethics Committee (REC), the Human Research Protection Program Institutional Review Boards (IRBs) at Yale University as well as by the Ghanaian Health Service Ethics Review Committee, which have reviewed the study protocols. Particular consideration will be given to potentially vulnerable people or groups, especially children, and informed consent will be acquired by Innovation for Poverty Action (IPA) staff from all parents of participating children before the commencement of any data collection, and that they can stop participating at any time without providing a reason. Model consent forms are available upon request. Any reports of abuse or dangers to children will be reported to relevant local authorities.

Important protocol modifications will be communicated to all relevant parties (eg, investigators, REC/IRBs, trial participants, trial registries, journals).

Data will be collected, handled, transferred and secured in a manner which aligns with international best practice. The IFS information security management system is ISO27001 compliant.

We will publish findings through (a) top academic journals in economics and developmental science; (b) presentations at conferences in Ghana, the USA and Europe; (c) publication of high-impact policy briefs for the wider public; (d) leaflets to communicate findings to participating communities; and (e) partner’s websites and social media.
